## Secondary outcome analysis

- The average LDQ after 12 weeks of oral administration of the investigational product: descriptive statistics (sample size, mean, standard deviation, median, min, max) will be presented for the LDQ score after 12 weeks of investigational product administration. The between-group difference will be tested for significance using the independent two-sample t-test or the Wilcoxon rank sum test.
- The average change in the GSRS from baseline after 12 weeks of oral administration of the investigational product: descriptive statistics (sample size, mean, standard deviation, median, min, max) will be presented for GSRS measured before and after 12 weeks of investigational product administration, and the change in GSRS from baseline after 12 weeks of oral administration of the investigational product in each treatment arm. The change within each arm will be tested for significance using the paired t-test or the Wilcoxon signed rank test. The between-group difference at each time point and in the amount of change will be tested for significance using the independent two-sample t-test or the Wilcoxon rank sum test.
- The incidence rate of GI adverse events (dyspepsia, diarrhea, nausea, abdominal pain, heartburn) after 12 weeks of oral administration of the investigational product: the number and proportion of the subjects who experience a GI adverse event during the 12 weeks of investigational product administration, and the frequency of these events, will be presented for each treatment arm. The between-group difference in proportion will be tested for significance using the Chi-square test or Fisher’s exact test.
- The discontinuation rate due to GI adverse events after 12 weeks of oral administration of the investigational product: the number and proportion of subjects who discontinue drug administration due to GI adverse events that occur during the 12 weeks of investigational product administration will be presented for each treatment arm. The between-group difference in proportion will be tested for significance using the Chi-square test or Fisher’s exact test.
- The average change in pain VAS from baseline after 12 weeks of oral administration of the investigational product: descriptive statistics (sample size, mean, standard deviation, median, min, max) for pain VAS before and after 12 weeks of investigational product administration, and the change in pain VAS from baseline after 12 weeks of oral administration of investigational product in each treatment arm, will be presented. The change within each arm will be tested for significance using the paired t-test or the Wilcoxon signed rank test. The between-group difference at each time point and in the amount of change will be tested for significance using the independent two-sample t-test or the Wilcoxon rank sum test.
- The average change in the average EQ-5D score from baseline after 12 weeks of oral administration of the investigational product: descriptive statistics (sample size, mean, standard deviation, median, min, max) for EQ-5D before and after 12 weeks of investigational product administration and the change in EQ-5D from baseline in each treatment arm will be presented. The change within each arm will be tested for significance using the paired t-test or the Wilcoxon signed rank test. The between-group difference at each time point and in the amount of change will be tested for significance using the independent two-sample t-test or the Wilcoxon rank sum test.
- Drug compliance after 12 weeks of oral administration of the investigational product: compliance during the 12 weeks of investigational product administration is defined by ‘actual number of administrations / predicted number of administrations *100’, and descriptive statistics (sample size, mean, standard deviation, median, min, max) will be presented for each treatment arm. The between-group difference in compliance will be tested for significance using the independent two-sample t-test or the Wilcoxon rank sum test. The actual number of administrations is determined based on the number of returned investigational products. Evident reasons, such as loss or damage, will be accounted for.
- Ancillary and rescue drug use after 12 weeks of oral administration of the investigational product, the average number of days used, the average daily amount used (total amount used / total number of days used), and the average amount of use during study participation (total amount used / study duration): the number and proportion of subjects who use ancillary or rescue drugs during the 12 weeks of investigational product administration are presented for each treatment arm. The between-group difference will be tested for significance using the Chi-square test or Fisher’s exact test. Descriptive statistics (sample size, mean, standard deviation, median, min, max) will be presented for the average number of days of ancillary or rescue drug use, the average amount used per day (total amount used / total number of days used), and the average amount used during the study period (total amount used / duration of study participation) in each treatment arm. The between-group difference in the average will be tested for significance using the independent two-sample t-test or the Wilcoxon rank sum test.
- The incidence, frequency, and characteristics (clinical presentation, severity, result, etc.) of adverse events after 12 weeks of oral administration of the investigational product: the number and proportion of subjects that experienced all adverse events, SAEs, and adverse events leading to study discontinuation during the 12 weeks of investigational product administration, as well as all adverse events, SAEs, and adverse events leading to study discontinuation that are related to the investigational product are presented for each treatment arm. The between-group difference in proportion will be tested for significance using the Chi-square test or Fisher’s exact test. The number of all adverse events and adverse events associated with investigational product, the severity and seriousness of these events, the treatment, and the results of the events will also be presented. The number and proportion of subjects, as well as the number of events for all adverse events and adverse events associated with the investigational product, as per MedDRA or WHOART SOC, and the PT, will also be presented for each treatment arm.
- Physical examination: a distribution chart that includes the frequency and proportion of normal and abnormal physical examination findings before and after the 12 weeks of investigational product administration will be presented. The significance of the change in each treatment arm will be tested using McNemar’s test or McNemar’s exact test, and the between-group difference in change will be tested for significance using the GEE (Generalized Estimating Equation).
- Vital signs: descriptive statistics (sample size, mean, standard deviation, median min, max) will be presented for vital signs before and after the 12 weeks of investigational product administration and for the change in vital signs after the 12 weeks of investigational product administration. The change in each treatment arm will be tested for significance using the paired t-test or the Wilcoxon signed rank test. The between-group difference at each time point and in the amount of change will be tested for significance using the independent two-sample t-test or the Wilcoxon rank sum test.
- Laboratory tests: a distribution chart that includes the frequency and proportion of normal and laboratory test findings before and after the 12 weeks of investigational product administration will be presented. The significance of the changes in each treatment arm will be tested using McNemar’s test or McNemar’s exact test, and the between-group difference in change will be tested for significance using the GEE (Generalized Estimating Equation). For continuous data, such as hematological or blood chemistry test results, descriptive statistics (sample size, mean, standard deviation, median, min, max) for values before and after the 12 weeks of investigational product administration, and the change in values after the 12 weeks of investigational product administration, will be presented. The change in each treatment arm will be tested for significance using the paired t-test or the Wilcoxon signed rank test. The between-group difference at each time point and in the amount of change will be tested for significance using the independent two-sample t-test or the Wilcoxon rank sum test.

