**Secondary purpose**

- To compare the gastroprotective effect, as evaluated by the Gastrointestinal Symptom Rating Scale (GSRS), of 12 weeks of treatment with Naxozol or celecoxib in osteoarthritis patients.
- To compare the incidence rate of gastrointestinal (GI) adverse events as well as the drug discontinuation rate due to gastrointestinal (GI) adverse events during 12 weeks of treatment with Naxozol or celecoxib in osteoarthritis patients.
- To compare the pain improvement effect, as evaluated by the visual analogue scale (VAS), after 12 weeks of treatment with Naxozol or celecoxib in osteoarthritis patients.
- To compare the improvement in quality of life (QoL), as evaluated by EQ-5D, after 12 weeks of treatment with Naxozol or celecoxib in osteoarthritis patients.
- To compare patient compliance during 12 weeks of treatment with Naxozol or celecoxib in osteoarthritis patients.
- To compare overall safety during 12 weeks of treatment with Naxozol or celecoxib in osteoarthritis patients.

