#### Control group

- Active control.
- This study will use the Celebrex capsule as an active control.

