## Inclusion criteria

- 1. Subjects of Korean nationality who voluntarily decide to participate in the study and provide written consent after receiving and understanding a detailed description and explanation of the study.
  2. Men and women aged 50 years or older at the time of consent.
  3. Persons who are available for follow-up throughout the study duration and are able to perform due tasks for the study, such as reading and filling out EQ-5D and VAS surveys.
  4. Persons with a confirmed medical history of physically symptomatic osteoarthritis who score 40 mm or greater on the pain VAS performed at V2.
  5. Persons deemed appropriate for the study based on the screening results (NB: subjects can be included at the discretion of the investigator even if laboratory test results are outside the reference ranges).

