#### Visit 2: Randomization visit (Day 1)

Visit 2 will be conducted on Day 1. The investigator will conduct the following procedures and evaluations for each subject:

- - Reconfirm the fulfillment of inclusion / exclusion criteria.
  - Conduct the pain VAS evaluation.
  - Conduct the LDQ evaluation.
  - Randomization.
  - Record all new adverse events and / or changes in pre-existing adverse events.
  - Record all co-administered drugs and / or changes in pre-existing co-administered drugs.
  - Distribute the GSRS and EQ-5D surveys and ask the subjects to answer them.
  - Distribute the investigational products.
  - Explain how to use the ancillary and rescue drugs, and how to fill out the subject log.
  - Distribute the ancillary and rescue drugs.
  - Confirm subject log completion and remind to bring the log at visit 3.
  - Book visit 3: the visit should be 84 days after visit 2 (Day 84 - 87).
  - Fill out the case report form.

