# Appendices

## Appendix 1. Study schedule

| Schedule | Screening & Washout period | | Treatment & Follow-up Period* | |
| --- | --- | --- | --- | --- |
|  | Screening1 | Randomization | | End of Study |
| Weeks | -2 - 0 | 0 | | 12 |
| Day of visit | -14 - 1 | 1 | | 84-87 |
| Visit category | V1 | V2 | | V3 |
| Consent |  |  | |  |
| Screening number assignment |  |  | |  |
| Inclusion / exclusion criteria |  |  | |  |
| Demographic information / medical history / medication history |  |  | |  |
| Physical examination 2 | (including weight) |  | |  |
| Vital signs3 |  |  | |  |
| X-ray (lesion)4 |  |  | |  |
| Pain VAS5 | - |  | |  |
| Randomization |  |  | |  |
| Blood test |  |  | |  |
| Blood chemistry test 6 |  |  | |  |
| Hematological test 7 |  |  | |  |
| Pregnancy test8 |  |  | |  |
| Drug administration |  |  | |  |
| Distribution of study drug / ancillary drug / rescue drug |  |  | |  |
| Collection of study drug / ancillary drug / rescue drug |  |  | |  |
| LDQ, GSRS, EQ-5D |  |  | |  |
| Distribution of subject log |  |  | |  |
| Collection of subject log |  |  | |  |
| Confirmation of co-administered drugs |  |  | |  |
| Adverse event monitoring |  |  | |  |

1. If additional washout is not needed, screening and randomization can be conducted on Day 1.
2. Height (history), weight (measured). Weight measured only at visit 1.
3. Blood pressure, pulse rate, respiration rate.
4. Not conducted if there is an X-ray result of the lesion taken within 6 months.
5. Conducted only at visit 2 and not at visit 1.
6. ALT, AST, BUN, creatinine, glucose, total bilirubin.
7. CBC (hemoglobin, hematocrit, RBC count, WBC with differential count, platelet count).
8. Conducted only in women of childbearing potential.

- **Additional visit**: Additional visits may be conducted if follow-up observation of adverse events is needed.

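### The within-arm tests of pain VAS change start from the score that selected the subjects, so a significant fall cannot be read as a drug effect

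*Protocol*

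**What the plan says.** The secondary purpose for pain (section 3) is comparative: "To compare the pain improvement effect, as evaluated by the visual analogue scale (VAS), after 12 weeks of treatment with Naxozol or celecoxib".

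Inclusion criterion 4 (section 4.3.1) admits persons with osteoarthritis "who score 40 mm or greater on the pain VAS performed at V2". Note 5 to the schedule in Appendix 1 says of the pain VAS: "Conducted only at visit 2 and not at visit 1". Section 6.1 lists one VAS evaluation at Visit 2 and one at Visit 3. The Visit 2 score is therefore both the entry score and the only baseline.

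Section 7.5.3 plans two kinds of inference on the change in pain VAS. Within arms: "The change within each arm will be tested for significance using the paired t-test or the Wilcoxon signed rank test". Between arms: "The between-group difference at each time point and in the amount of change will be tested for significance using the independent two-sample t-test", with the Wilcoxon rank sum test as the alternative. Section 7.5.1 puts all tests other than the primary one at a two-sided 5% level and gives the within-arm tests no lower standing. On the comparator, section 4.1 says: "This study will use the Celebrex capsule as an active control".

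**The concern.** A paired test asks whether the mean at Visit 3 differs from the mean at Visit 2. Its natural reading is that the drug relieved pain. That reading needs a reference for what would have happened without the drug, and this trial has none.

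The entry rule makes the gap worse. Some subjects who score 40 mm or more on the day do so partly because that day was a bad one. Their next score tends to be lower whatever they take. The V2 mean is raised by selection, the V3 mean is not, and the paired test counts the difference as change. Rescue acetaminophen (section 5.3.1.2) also contributes to the within-arm change.

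Pain relief is in the trial's title, so a significant p-value within an arm could be reported as efficacy although it does not address the comparative objective.

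**Working it through.** **The plan's own figure.** The only sample size in the protocol is for LDQ (section 7.1): 2 × 0.65² × (1.96 + 0.842)² / 0.4² = 41.46, rounded up to 42 per arm; 42 / 0.8 = 52.5, rounded up to 53. Both reproduce. I use n = 42 below. Nothing comparable is stated for pain VAS.

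**Assumptions.** The protocol gives no VAS mean, SD or correlation between visits, so these are assumed. The V2 and V3 scores in the unselected population are taken as bivariate normal with the same mean and SD, correlation r, and no drug effect. Subjects enter if V2 is at least 40 mm.

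**Expected fall with no drug effect.** With a = (40 − mean)/SD and λ = φ(a)/(1 − Φ(a)):

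fall = (1 − r) × SD × λ

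For mean 50, SD 20, r = 0.7: a = −0.5, λ = 0.3521/0.6915 = 0.509, fall = 0.3 × 20 × 0.509 = 3.05 mm.

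**Precision of the paired test.** The variance of V2 after selection is SD²(1 + aλ − λ²) = 400 × (1 − 0.2546 − 0.2592) = 194.5. The variance of change is (1 − r)² × 194.5 + SD²(1 − r²) = 17.5 + 204 = 221.5, so the SD is 14.9 mm and the standard error is 14.9/√42 = 2.30 mm.

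**Chance of a significant fall.** The non-centrality is 3.05/2.30 = 1.33. With 41 degrees of freedom the critical value is 2.02, and the non-central t distribution gives 25%. Direct simulation of 4,000 trials gave 26% at n = 42 and 31% at n = 53.

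| Mean, SD, r (assumed) | Expected fall, mm | Chance of a significant fall per arm, n = 42 |
|---|---|---|
| 60, 15, 0.8 | 0.5 | 6% |
| 60, 20, 0.7 | 1.7 | 11% |
| 55, 20, 0.6 | 3.1 | 21% |
| 50, 20, 0.7 | 3.05 | 25% |
| 50, 20, 0.5 | 5.1 | 41% |

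The nominal chance in that direction is 2.5%. Simulations of these cases agree to within about two percentage points. Over a wider grid (mean 40 to 60, SD 15 to 25, r 0.5 to 0.9) the fall runs from 0.3 to 10.0 mm and the chance from about 5% to about 80%. The upper end needs a population mean right at the 40 mm threshold.

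**The between-arm test.** In the same simulations, the two-sample t-test of change rejected in 4.2% to 5.7% of trials across every scenario, against a nominal 5%. Both arms regress by the same expected amount and the difference cancels.

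**What adjustment adds.** In an ANCOVA on the V2 score the residual variance is SD²(1 − r²). In the 50, 20, 0.7 case that is 204 instead of 221.5, a reduction of 17.5/221.5 = 7.9%. Across the five cases the reduction is about 7% to 14%.

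**The case against.** The strongest reply is that the right analysis is already in the plan. The between-group test of the amount of change answers the stated objective, and randomisation protects it. This stands. A reader might infer from the selection argument that the trial's pain comparison is biased. The documents do not support that, because the same entry rule applies to both arms.

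Second, section 7.5.3 tests change, not drug effect. As a test of zero mean change the paired test does what it says, and no decision rule rests on its p-value. This also stands. The fault lies in giving a 5% significance test, with no descriptive label, to a quantity that cannot support the conclusion usually drawn from it.

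Third, a null in which neither drug works is remote: section 2.9 treats NSAID efficacy for osteoarthritis pain as accepted, and section 4.2.3 describes both doses as locally approved. That lowers the practical harm. It also means the within-arm tests answer no question the trial is asking.

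Fourth, every percentage rests on assumed VAS values. Subjects need NSAID therapy and must have been off NSAIDs for 7 days, so a mean well above 40 mm is plausible, and the inflation is then small. The 25% and 41% figures are illustrations, not properties of this trial.

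Fifth, a reader might extend the argument to GSRS and EQ-5D, which have the same within-arm tests. Subjects were not selected on those scores, so the selection argument does not reach them. Only the absence of a placebo reference does.

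**Conclusion.** The point holds in a limited form. The single V2 score serves as both entry criterion and baseline, and no arm shows the course without active drug, so a significant within-arm fall in pain VAS cannot be read as a drug effect. With no drug effect it would appear in roughly 5% to 40% of arms under the tabulated assumptions, against a nominal 2.5%. The size depends on VAS parameters that the protocol does not give.

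The consequence is minor. Pain VAS is a secondary endpoint, the between-arm test of change keeps its level, and the LDQ analysis and its sample size are untouched.

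**What to change.** In section 7.5.3, under pain VAS:

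- Replace the within-arm paired t-test or signed rank test with the mean change in each arm and its 95% CI, labelled descriptive.
- State that the pain objective is judged only on the between-arm difference in VAS change with its 95% CI, from an ANCOVA adjusted for the V2 score, in place of the unadjusted t-test or rank sum test. The adjustment is for precision; the unadjusted comparison is already unbiased.

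For GSRS and EQ-5D, labelling the within-arm results as descriptive is optional and rests only on the lack of a placebo reference.

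The cost is wording and the loss of the within-arm p-values for VAS. No extra data, visits or subjects are needed, because the V2 score is already collected.

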## Rationale for administration of the investigational product to the study subjects

Symptoms of dyspepsia associated with NSAID use are very common and are reported to occur in 20-25% of NSAID users. (11,12,13,14) However, 40% of NSAID users with endoscopically confirmed erosive gastritis did not show symptoms of dyspepsia, and 50% of patients with symptoms of dyspepsia have normal gastrointestinal mucosa, indicating that symptoms of dyspepsia do not predict damage to gastrointestinal mucosal lining. (11,13,14,15) When compared to non-selective NSAID use, COX-2 inhibitor use is reported to decrease the symptoms of dyspepsia associated with NSAID use. (11,16,17)

Additionally, symptoms of dyspepsia associated with non-selective NSAID use can be reduced with PPIs. PPIs such as omeprazole or esomeprazole are reported to be more effective in symptomatic improvement of dyspepsia than ranitidine or misoprostol. (13,14,18,19)

Therefore, to adequately consider both treatment-related efficacy and safety, either Naxozol tablets or a COX-2 inhibitor were administered to the osteoarthritis patients participating in this study.

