## Secondary evaluation

As secondary evaluation endpoints, the GSRS, pain VAS, and EQ-5D will be used.

- The GSRS (Gastrointestinal Symptom Rating Scale) consists of 15 short answer questions that can indicate a high correlation with gastroesophageal reflux disease, functional dyspepsia, and irritable bowel disease. (26, 27, 28)
- The VAS (visual analogue scale) will be used to evaluate the osteoarthritic pain experienced by the subjects. The VAS is a simple method that is widely used for pain evaluation in osteoarthritis patients. It has proven correlation with the survey-based Likert scale. (29)
- EQ-5D is a widely-used tool for the measurement of quality of life and health status. It includes the five categories of mobility, self-care, usual activities, pain / discomfort, and anxiety / depression. Each item is measured using the VAS, indicating subjective health status on a thermometer-shaped scale, as well as by multiple choice questions that evaluate health status as one of the following three stages: “no problem”, “some problems”, and “extreme problems”.

The study will also evaluate the incidence rate of gastrointestinal adverse events and the discontinuation rate due to gastrointestinal adverse events.

As an ancillary method to evaluate the pain control of the experimental drug and comparator, this study will also evaluate ancillary and rescue drug use after 8 weeks of oral administration of the study drugs, the average number of days of use, the average amount used per day (total amount used / days used) and the average amount of use during the study period (total amount used / study duration).

This study will also include compliance analysis. Compliance is defined as ‘(the actual number of administrations) / (the planned number of administrations)*100’, and patients with a compliance rate of 80% or above will be included in the PP (per-protocol) group analysis.

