## Secondary evaluation endpoint

- Average LDQ after 12 weeks of oral administration of the investigational product.
- Average change in the GSRS from baseline after 12 weeks of oral administration of the investigational product.
- Incidence rate of GI adverse events (dyspepsia, diarrhea, nausea, abdominal pain, heartburn) after 12 weeks of oral administration of the investigational product.
- Discontinuation rate due to GI adverse events after 12 weeks of oral administration of the investigational product.
- Average change in the pain VAS from baseline after 12 weeks of oral administration of the investigational product.
- Average change in the average EQ-5D score from baseline after 12 weeks of oral administration of the investigational product.
- Drug compliance after 12 weeks of oral administration of the investigational product.
- Ancillary and rescue drug use after 12 weeks of oral administration of the investigational product: average number of days used, average daily amount used (total amount used / total number of days used), and average amount of use during study participation (total amount used / study duration).
- Incidence, frequency, and characteristics (clinical presentation, severity, result, etc.) of adverse events after 12 weeks of oral administration of the investigational product.
- Results of physical examination, vital signs, and laboratory tests after 12 weeks of oral administration of the investigational product.

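### Ancillary and rescue drug amount per day of use is undefined for non-users, so its planned between-arm test compares only a subset selected after randomisation (minor)

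*Protocol*

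**What the plan says.** The measure appears in four places: the Synopsis (secondary outcomes), 6.4.2, 7.3.2 and 7.5.3. Section 7.3.2 has "average daily amount used (total amount used / total number of days used", section 6.4.2 has "the average amount used per day (total amount used / days used", and section 7.5.3 has "the average amount used per day (total amount used / total number of days used". Each time it stands beside a separate measure that divides the same total by study duration or duration of participation.

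Section 7.5.3 then fixes the analysis. Each arm is summarised: "Descriptive statistics (sample size, mean, standard deviation, median, min, max) will be presented for the average number of days of ancillary or rescue drug use", and likewise for the two amount measures. After that, "The between-group difference in the average will be tested for significance using the independent two-sample t-test or the Wilcoxon rank sum test".

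The same bullet expects non-users, because "the number and proportion of subjects who use ancillary or rescue drugs during the 12 weeks of investigational product administration are presented for each treatment" group, with a chi-square or Fisher test. No rule is given for a subject with zero days of use. Section 7.5.1 says only that missing data will be multiply imputed, with no exception for ratios that cannot be formed.

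**The concern.** A measure that exists only for people who took the drug is given a between-arm significance test. Whether a subject takes almagate or acetaminophen is decided after randomisation and depends on symptoms: 5.3.1.1 allows almagate for severe dyspepsia, and 5.3.1.2 allows acetaminophen when pain control is difficult. Both symptoms are what the study drugs are meant to affect. The users in each arm are therefore selected partly by treatment, and randomisation does not make them comparable.

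If one drug spares patients with mild symptoms from needing any tablets, the users left in that arm are the heavier ones. Their average per day of use rises, and the arm that prevented use can appear to need more. Section 6.4.2 presents these measures as a supporting way to judge pain control, so such a result would probably be read as evidence about treatment.

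**Working it through.** **Inputs.** Margin 0.4, SD 0.65, one-sided alpha 0.025, power 80%, drop-out 20% (7.1). Formula and test for the daily amount (7.3.2, 7.5.3). Treatment period 84 days (6.1). The share of users is not in the protocol and is assumed below.

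**1. The plan's own figure.** n = 2 × 0.65² × (1.96 + 0.842)² / 0.4² = 41.46, rounded up to 42 per arm. 42 / 0.8 = 52.5, rounded up to 53. Both figures reproduce, and neither depends on this measure.

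**2. Value for a non-user.** The plan lists one amount divided by days used and another divided by duration of participation. The first denominator must therefore be days of ancillary or rescue use. For a non-user the amount is 0 and the days are 0, giving 0/0, which is undefined.

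**3. What the test can then act on.**
- *Users only.* This follows from the formula as it stands.
- *Imputed values.* Treating 0/0 as missing under 7.5.1 would assign a per-use-day dose to people with no use-days.
- *Non-users set to 0.* The protocol does not say this, and the result would no longer be an amount per day of use.

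**4. Can the direction reverse?** An illustration with assumed usage, 53 per arm. Arm A has 10 users, each taking 3 tablets a day on 10 days. Arm B has 10 identical users plus 20 lighter ones taking 1 tablet a day on 10 days.

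| Measure | Arm A | Arm B | Lower use in |
|---|---|---|---|
| Amount per use-day, users only | 30/10 = 3.00 | (10×3 + 20×1)/30 = 1.67 | B |
| Proportion using | 10/53 = 19% | 30/53 = 57% | A |
| Mean days used, all subjects | 100/53 = 1.9 | 300/53 = 5.7 | A |
| Amount per study day, all subjects | 300/(53×84) = 0.067 | 500/(53×84) = 0.112 | A |
| Amount per use-day, non-users at 0 | 30/53 = 0.57 | 50/53 = 0.94 | A |

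The users-only Wilcoxon test gives p = 0.0003 (corrected for ties) against arm A. Amount per study day gives p = 0.002 and Fisher's test on proportion using gives p = 0.0001, both in favour of A.

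**5. Reversal is possible, not certain.** In a simulation with 53 per arm, treatment cut the share of users from 50% to 31%, and tablets per use-day did not depend on severity. Mean amount per use-day among users was 1.98 against 1.97. The users-only t-test rejected in 5% of runs, its nominal level, against 42% for amount per study day. Here the measure does not mislead; it simply misses the effect.

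**6. How many subjects have a value.** For an assumed share of users u, about 53u per arm:

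| Assumed share using | With a value, of 53 |
|---|---|
| 20% | 11 |
| 30% | 16 |
| 50% | 26 |
| 70% | 37 |

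**The case against.** The strongest reply is that the same bullet already plans three measures that can be defined for everyone: proportion using, days used, and amount over duration of participation. Dose on days of use is a natural companion to how many used the drug, and in the illustration the other results point the right way. A reader would be misled only by taking one of four adjacent results alone. This stands, and it is why the point is minor.

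A second reply is that handling of non-users belongs in a statistical analysis plan, which is not shown. The protocol does not say that non-users are excluded, and a zero rule would restore the direction in the illustration (0.57 against 0.94). This stands only in part. The protocol itself fixes both the ratio and the between-arm test, and setting non-users to 0 would replace the stated ratio with a different quantity.

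Three stronger readings are tempting but not supported:

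- *Most of the sample is lost.* Section 2.6 says dyspepsia symptoms "are reported to occur in 20-25% of NSAID users", which might be taken as the share using almagate. That figure concerns dyspepsia in NSAID users generally. Section 2.6 also says that COX-2 inhibitors and PPIs reduce these symptoms, and 5.3.1.1 reserves almagate for severe ones. No share is given for acetaminophen. With entry at a pain VAS of 40 mm or more and prior NSAIDs washed out, its use could be common.
- *The detectable difference rises by a stated number of SDs.* Setting a standardised difference for all subjects beside one for users compares two variables with different SDs, so the figures are not like for like.
- *The better drug will look worse.* The illustration shows only that it can; step 5 shows a case where it does not.

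**Conclusion.** The concern holds as a minor point. The measure is undefined for any non-user, and the planned between-arm test on it therefore falls on a subset formed after randomisation and shaped by treatment, or else on imputed doses that never existed. Both conclusions follow from the stated formula and test, whatever the share of users.

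The practical size is unknown. Between 11 and 37 of 53 per arm would have a value if 20% to 70% used the drug, and that range is an assumption. The illustration and the simulation also rest on assumed usage. The consequence is confined to one component of one of the ten secondary endpoints in 7.3.2. A reader might infer that the trial's main conclusion is at risk, but the primary LDQ analysis and the sample size are untouched.

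**What to change.** Make the same change in the Synopsis, 6.4.2, 7.3.2 and 7.5.3; editing only the last two would leave the document inconsistent.

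- Report amount per day of use descriptively among users, with the number of users shown in each arm and no between-arm test. State that a non-user's value is not applicable, so the imputation rule in 7.5.1 does not reach it.
- Base the arm comparison on proportion using, number of days used, and amount divided by duration of participation, in all subjects, with non-users counted as 0 for the last two.

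A zero rule for amount per use-day would also make the test computable. However, the result would mix whether a subject used the drug with how much was taken on days of use, and the measures above already cover overall use more clearly.

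The cost is a wording change and the loss of one significance test per drug. No new data are needed, and the way the two drugs are given is not affected.
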